## Abstract

**Background:** The last few decades people have increasingly started to use technological tools for health and activity monitoring, such as tracking apps and wearables. The main assumption is that these tools are effective in reinforcing self-empowerment because they support better-informed lifestyle decision-making. However, experimental research assessing the effectiveness of the technological tools on such psychological outcomes is limited.

**Methods and Design:** Three studies will be conducted. First, we will perform a systematic review to examine the experimental evidence on the effects of self-tracking apps on psychological outcome measurements. Second, we will conduct a longitudinal field experiment with a between subject design. Participants (*N* = 150) begin a 50-day exercise program, either with or without the aid of the self-tracking app Strava. Among those who use Strava, we vary between those who use all features and those who use a limited set of features. Participants complete questionnaires at baseline, at 10, 25, and 50 days, and provide details on what information has been tracked via the platform. Third, a subset of participants is interviewed to acquire additional qualitative data. The study will provide a rich set of data, enabling triangulation, and contextualization of the findings.

**Discussion:** People increasingly engage in self-tracking whereby they use technological tools for health and activity monitoring, although the effects are still unknown. Considering the mixed results of the existing evidence, it is difficult to draw firm conclusions, showing more research is needed to develop a comprehensive understanding.

**Trial registration:** Netherlands Trial registration: NL9402, received on 20 April 2021; https://www.trialregister.nl/trial/9402.

## Introduction

People increasingly use technological tools for health and activity monitoring (1–4). These activity tracking apps and wearables are considered self-empowering because they can help users make better-informed lifestyle decisions based on their data (5, 6). Recent research, however, suggests that self-tracking technology use may lead to bodily *alienation* rather than empowerment, because it could encourage users to trust technology more than what their own body tells them (7). Because these technologies make explicit all sorts of bodily experiences and processes that would otherwise remain unnoticed (heart rate, burned calories, etcetera), people might develop a more objectified and distant instrumental view on their body as something that needs to be monitored and corrected—at the cost of a tacit, smooth reliance on it (5).

To date, however, there is no empirical research, at least to our knowledge, that examines the mechanisms leading to either bodily empowerment or alienation. This protocol describes the uses of different methodological approaches that we will conduct in a project to investigate under which conditions the use of a self-tracking app fosters bodily empowerment or bodily alienation. More specific, the main objective that this project will study is whether and under which conditions the use of self-tracking technologies empowers or alienates people while doing physical activity.

Collecting health related data with technological tools and platforms is referred to as “self-tracking for health” (5, 7). Self-tracking for health involves a self-monitoring process that relies on the quantification of bodily processes (e.g., heart rate, calories burned) and activities (e.g., step counts, types of sports). People have been self-monitoring their body and life for self-improvement since ancient times (8), although with the introduction of digital technologies, users can (1) collect personal and health data in real-time and at a much larger scale, (2) gain information on parameters that are difficult—if not impossible—to track otherwise, (3) obtain personalized feedback and gamified targets derived from processing of collected data (7), and (4) link their data to other data streams, such as social networking platforms, enabling them to compare with others (4).

There is a widespread belief among technology developers, health professionals and scholars that self-tracking technologies can empower users to make healthier life choices (7–9). For example, following Deci and Ryan's (10). Self-Determination Theory, it is argued that self-tracking technologies fulfill the three needs for empowerment: (1) autonomy, (2) competence, and (3) belongingness. Self-tracking technologies allow users to regulate their physical activity without having to rely on external parties (autonomy), help them reach personal targets and compare their performance with others (competence), and generate belongingness through online endorsements and commenting features (11).

Given their assumed empowering potential, one might expect spectacular usage rates for self-tracking technologies. Recent intervention studies, however, report significant numbers of drop out (11–14), with over 50% of new users dropping out in <2 weeks (6). An explanation for this drop-out might be that some users experience *bodily alienation* rather than bodily empowerment (15). This study adopts a multi-method approach to examine if the use of self-tracking technologies lead to bodily alienation rather than bodily empowerment, and whether these in turn predict future use of self-tracking technology as well as future exercise behavior.

Classical phenomenological theories (16–18) shed light on this possibility. They emphasize that in our normal interactions with the world, our bodies function “transparently”: we are typically not aware of our bodies functioning, such as our hearts beating or our feet moving. Scholars argue that paying conscious attention to these tacit bodily processes may have a disruptive, alienating effect on individuals, because such “hyperreflectivity” (16) disturbs our effortless, smooth flow of acting, like paying attention to your feet disrupts your dancing moves. In reflectively engaging with our bodies, then, we may come to see our bodies as objects or instruments to be tweaked and altered, rather than functioning in the background of our everyday existence.

## Methods and Analysis

In total, three separate studies will be conducted in this project, see for a detailed timeline and phases of the study in Figure 1. First, we will perform a systematic review to examine the experimental evidence on the effects of self-tracking apps on psychological outcome measurements linked to bodily empowerment and alienation to have a state of the art understanding in this area. Second, we will conduct a longitudinal field experiment with a between subject design. Third, a subset of participants is interviewed to acquire additional qualitative data. The study will provide a rich set of data, enabling triangulation, and contextualization of the findings to provide an answer to our research questions. We will provide some more detailed information on the three separate studies here.

**Figure 1 F1:**
[figure not shown]
Enrolment, interventions, and assessment in the study period.

### Study 1: Systematic Review

First, to have a state-of-the-art understanding of current existing causal evidence we will conduct a systematic review focusing on experimental studies. As a result of the systematic review we will develop detailed hypotheses that we will test in Study 2: An experimental study and Study 3: Interviews. Participants will be blinded to the hypotheses. We will investigate the following bibliographic databases: PubMed, PsychInfo, and ISI Web of Science, whereby we will restrict our search to peer-reviewed papers or dissertations written in English in the last 10 years (>2010). Next, we will do a manual search in selected articles' reference lists to make sure we do not miss any relevant studies. Studies will be considered eligible if they; (1) report experimental effects of the usage of self-tracking technologies on psychological outcomes, (2) include self-tracking among healthy people and people of any gender and age diagnosed with any type of (chronical) disease, and (3) use self-tracking technologies on one of the following devices for self-tracking; mobile (smart)phones and applications, and/or wearables. Studies will be excluded if they are published before 2010, are not peer-reviewed, are written in a non-English language and have a non-experimental design. The primary outcomes from this systematic review will be used to develop the exact experimental design. For the systematic review, we will follow the PRISMA standard guidelines whereby we provide a detailed explanation to improve transparency. In addition, we will present a flow diagram with all the selection steps of the process and the exclusion criteria.

### Study 2: Experimental Study

Second, we will conduct a longitudinal (50 days) field experiment with a between subject design, aiming for 150 participants that we will collect based on convenience sampling at the Tilburg University campus, see also Recruitment section. We will pre-register our trial (www.trialregister.nl) before we start collecting data and we will include the CONSORT and SPIRIT-statements in our reporting of the outcomes of this study. In this study, we will create two groups that we will randomly allocate to using Strava or not for their physical activity tracking, randomly assigned based on enrolment. An eligibility criterion to participate in the study is that participants must not have used self-tracking technologies for at least 2 months before starting the experiment. Participants complete questionnaires at baseline, after 10 days, 25 days, and a final one after 50 days. We will ask participants to provide details on what information has been tracked via the platform. Next, a subset of participants is interviewed (Study 3).

Power analyses (G^*^Power) (19) with an *F*-test (MANCOVA), suggest that a sample size of *N* = 148 is expected to be sufficient to detect significant (α = 0.05), medium effects (*f* = 0.25) of conditions (power = 0.80). We have based the medium effect size on the study of Seo et al. (20). Considering that some participants might drop out before the last measurement after 50 days, the plan is to include more than 150 participants in the study. We will conduct Multivariate analysis of (Co-)Variance to analyse the primary and secondary outcomes of the experiment.

In the experiment we will repeatedly collect different information (see also Figure 2), for example the primary outcomes the motivation to conduct physical activities and psychological need satisfaction, and the secondary outcomes self-reported physical activity, engagement in physical activity, enjoyment of physical activity, experiences of bodily alienation-empowerment, physical body experience, objectified body consciousness, self-objectification, wearable technology trust, wearable technology motivation, and trust in Strava. We will only use validated scales to assess these factors, and will conduct Factor Analysis and Reliability Analyses to make sure the scales we will use are valid and reliable in our dataset as well. All functionalities within Strava, using GPS for recording your physical activities, connecting to people to share recordings of physical activity, comment, or like physical activities of others or see reactions of others on your recordings, share and detect routes, trainings, races, and challenges with your network, connect to a (local) club or community, share photo's, and track and receive feedback on level of fitness and progress, will be part of the study. No specific assessment is considered to be more relevant than other information because the current study will mainly be conducted to test the differences between participants who use a self-tracking app compared to participants who do not use a self-tracking app. In future studies more attention could be given to different functionalities and see the effects of these on psychological or physiological outcomes.

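### Control is defined as not using Strava, but the stated contrast is app versus no app, so control use of another tracker is neither excluded nor visibly recorded

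*Protocol article*

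**What the plan says.** The article describes the comparison in three places.

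- **Abstract:** participants exercise for 50 days "either with or without the aid of the self-tracking app Strava".
- **Study 2: Experimental Study, allocation:** two groups are formed, which the investigators will "randomly allocate to using Strava or not for their physical activity tracking".
- **Study 2: Experimental Study, statement of what is tested:** people who use a self-tracking app are compared with "participants who do not use a self-tracking app".

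Tracker use is limited in two places. Study 2 requires no self-tracking technology in the two months before the start. Recruitment excludes people who already track their activity. Neither extends into the 50 days.

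On recording, Study 2 asks participants what was tracked via the platform. The outcomes it lists as examples include trust in and motivation from wearable technology, but no item on whether a control used a tracker.

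**The concern.** The Abstract and the allocation sentence define control by the absence of one product. The statement of what is tested defines it by the absence of any self-tracking app. A non-user of Strava who starts another app or wearable on, say, day 3 satisfies the first definition and fails the second.

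The article itself gives a reason why this matters. Under Generalizability it expects its results to extend to other self-trackers with similar functions. If so, a control who uses one receives some of the effect under study, and the difference between allocated groups shrinks toward zero. If the use is not recorded either, a small or null difference would be hard to interpret. It could mean that tracking has little effect, or that some controls were tracking too.

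**Working it through.** **1. The definitions side by side**

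| Control participant during the 50 days | Abstract and allocation sentence | Stated contrast |
|---|---|---|
| Uses no tracker | complies | valid control |
| Uses Strava | does not comply | not a valid control |
| Uses another self-tracking app | complies | not a valid control |

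The third row is the gap. The entry rules do not close it, because they concern use before or at entry. The platform data do not reveal it, because a control using a different product leaves no record on Strava.

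**2. Inputs for an illustration of size**

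- From Study 2: the plan is to "detect significant (α = 0.05), medium effects (*f* = 0.25) of conditions (power = 0.80"), and a "sample size of *N* = 148 is expected to be sufficient".
- Assumed: two equal groups (74 each; no allocation ratio is given) and a univariate F-test. The article names "Power analyses (G^*^Power) (19) with an *F*-test (MANCOVA") without giving the number of groups, covariates or responses entered.
- Assumed: a share c of controls uses another tracker, and that tracker has a fraction r of the Strava effect. The documents give neither c nor r.

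**3. The plan's own figure**

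A two-group univariate F-test with f = 0.25, alpha 0.05 and power 0.80 needs N = 128, and three groups need 158. Neither is 148, so the stated N is not reproduced from the inputs given. That is a separate matter. It does mean that the figures below illustrate dilution and do not restate the planned MANCOVA power.

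**4. Formula**

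If a share c of controls receives a fraction r of the effect, the control mean moves by c × r of the full difference, so

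effective f = 0.25 × (1 − r × c).

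Power comes from the non-central F distribution with 1 and 146 degrees of freedom and non-centrality λ = 148 × (effective f)². Without contamination, λ = 148 × 0.0625 = 9.25 and power is 0.856.

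Worked example, c = 20%:

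- r = 1: f = 0.25 × 0.80 = 0.200, λ = 148 × 0.0400 = 5.92, power 0.676.
- r = 0.5: f = 0.25 × 0.90 = 0.225, λ = 148 × 0.050625 = 7.49, power 0.776.

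**5. Results**

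| Controls using another tracker (c) | Power, full Strava effect (r = 1) | Power, half effect (r = 0.5) |
|---|---|---|
| 0% | 0.86 | 0.86 |
| 5% | 0.82 | 0.84 |
| 10% | 0.78 | 0.82 |
| 20% | 0.68 | 0.78 |
| 30% | 0.56 | 0.73 |

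At full effect, power passes below 0.80 between 7% and 7.5% contamination: 5 of 74 controls leave 0.804 and 6 of 74 leave 0.793. At half effect the crossing is at twice that share, between 14% and 15%.

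**The case against.** The strongest reply is that the sections should be read together. Non-trackers are recruited and then either start Strava or carry on as they were, and the statement of what is tested does call the comparison group non-users. On that reading the intention is clear and the wording merely loose. Control instructions and adherence items also belong naturally in a full protocol, which is not shown. The list of measures is introduced as examples, and it refers to a timetable figure that is not available here.

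Much of this stands. It would be wrong to say that control is defined only as not using Strava. It would also be wrong to say that tracker use will certainly go unrecorded. What remains does not depend on an omission: two statements of the comparison, both in print, classify the same participant differently.

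A reader might also infer from the power figures that the trial is underpowered through contamination. The documents do not support that.

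- No contamination rate is given, and excluding recent tracker users should lower it. At 5% with full effect, power is still 0.82.
- The full-effect column is an upper case. Strength and Limitations says Strava has functions that other apps lack, and Study 2 counts social features as part of the exposure. A passive phone step counter has few of these.
- The calculation is univariate with two groups. The planned test is a MANCOVA, and the Abstract adds a split within the Strava group ("we vary between those who use all features and those who use a limited set of features").

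**Conclusion.** The point holds as an inconsistency in the control definition. The Abstract and the allocation sentence describe Strava versus no Strava, while the stated test is app versus no app. Nothing described in the article limits or reveals other tracker use by controls during the 50 days.

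The consequence is possible dilution of unknown size. Under the assumptions above, contamination of 10% to 30% would bring power from 0.86 to between 0.78 and 0.56 at full effect, and to between 0.82 and 0.73 at half effect. The direction, toward zero, rests on other trackers acting in the same direction as Strava, which is the article's own view under Generalizability.

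A reader might go further and conclude that a null result could not be told apart from contamination. That needs certainty that tracker use is not recorded, and an illustrative list of measures cannot give it. The change is worth making because it is cheap and aligns the trial with its own question.

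**What to change.** 1. **Align the definitions.** In the Abstract and the allocation sentence, define control as not using any self-tracking app or wearable to track physical activity during the 50 days, so that allocation and stated contrast name the same comparison.
2. **Record use.** At days 10, 25 and 50, ask all participants in every group which trackers they have used since the last questionnaire, including whether they looked at a built-in phone counter. Record phone counters rather than bar them, since they may run passively and a ban would be impractical.
3. **Analyse by allocation.** Keep contaminated controls in the group to which they were randomised, because dropping or reclassifying them would break the randomised comparison. Report the contamination rate by arm. An adherence-adjusted estimate is optional and supportive only.

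The cost is a line in the control definition and one item in three questionnaires already planned. The downside is small: asking about trackers may draw controls' attention to them.

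### MANCOVA as the only named analysis, with a larger sample as the only stated answer to drop-out, leaves the Strava comparison at avoidable risk of bias; a repeated-measures mixed model is a cheap improvement

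*Protocol article*

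**What the plan says.** All quotes are from the protocol article.

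- **Waves.** Study 2: Experimental Study states: "Participants complete questionnaires at baseline, after 10 days, 25 days, and a final one after 50 days".
- **Analysis.** The same section names one method for every outcome: "We will conduct Multivariate analysis of (Co-)Variance to analyse the primary and secondary outcomes of the experiment". It does not say how the waves enter the model.
- **Drop-out.** The section expects some loss: "Considering that some participants might drop out before the last measurement after 50 days". Its response is a larger sample: "the plan is to include more than 150 participants in the study". It gives no rate and no other remedy.
- **Possible cause.** The Introduction, discussing high drop-out in other studies and among new users, says: "An explanation for this drop-out might be that some users experience" bodily alienation. It also asks, of alienation and empowerment, "whether these in turn predict future use of self-tracking technology as well as future exercise behavior".
- **Outcomes.** Study 2 lists motivation and psychological need satisfaction as primary. Experience of bodily alienation-empowerment is secondary.
- **Comparison.** Study 2 allocates people at random to use Strava or not. It later describes the purpose as to "test the differences between participants who use a self-tracking app compared to participants who do not use a self-tracking app".

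**The concern.** Standard MANOVA and MANCOVA remove a person who lacks any response in the model. With several waves as joint responses, one missed questionnaire is enough. With day 50 analysed alone, anyone who left earlier is lost, and the earlier answers that could have informed the estimate go unused.

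Loss unrelated to the outcome would cost only precision, and a larger sample would be a fair answer. The Introduction, however, raises the possibility that app users leave because they feel alienated. The people missing from the Strava arm would then be those with the worse scores, with no matching selection among controls. The remaining Strava users would look better than the arm as randomised. Recruiting more people under the same process gives a more precise estimate with the same bias. What is at stake is whether the trial can detect alienation, one of the two effects it was set up to study.

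**Working it through.** **Planned effect as a yardstick.** Study 2 gives f = 0.25, α = 0.05, power 0.80 and N = 148. For two groups d = 2f = 2 × 0.25 = 0.5. With noncentrality f²N, a plain F-test needs N = 128 for two groups and 158 for three. The stated 148 is therefore not reproduced from the stated inputs. That is a separate matter and does not affect this point.

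**What a larger sample does.** To keep 148 completers, enrolment must be 148 / (1 − loss):
- 10%: 148 / 0.9 = 165
- 20%: 148 / 0.8 = 185
- 30%: 148 / 0.7 = 212
- 50%: 148 / 0.5 = 296

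If each of the three follow-up waves independently lost 10%, 0.9³ = 72.9% would have complete data, or 109 of 150. This concerns precision only.

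**Bias, single drop-out step (assumed inputs).** Scores are in SD units with higher meaning better. Correlation between waves is ρ = 0.6. Strava-arm loss after day 10 has log-odds rising by 0.5 to 1.5 per SD worse day-10 score. Control loss is random at 15%. The analysis is a day-50 ANCOVA on completers, adjusted for baseline.

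A hand check at 50% loss and slope 1, true effect zero:
- Let m be the mean day-10 score of those who stay. With a standard normal score X and logistic retention, m = E[X·logistic(X)] / 0.5 = 0.207 / 0.5 = 0.41.
- Their day-50 and baseline means both shift by ρm.
- Adjusting for baseline removes ρ × ρm, leaving a bias of ρ(1 − ρ)m = 0.6 × 0.4 × 0.41 = 0.10 SD.

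Simulation agrees. A true 0 is estimated as +0.10, and a true −0.30 as −0.20. Using the day-10 scores of drop-outs returns −0.30. Over slopes 0.5 to 1.5:

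| Strava-arm loss | Completer bias (SD) | As share of d = 0.5 |
|---|---|---|
| 10 to 30% | about 0.01 to 0.08 | 2 to 16% |
| 50% | about 0.06 to 0.13 | 12 to 26% |

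With slope zero the bias is zero.

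**Would using all waves cure it?** A second simulation used four waves, ρ = 0.6, a true effect of zero, slopes 0.5 to 1.0 and random control loss at the same nominal rate. Bias in SD:

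| Nominal loss | Loss depends on previous observed score: completers | Same: all waves | Loss depends on unobserved current score: completers | Same: all waves |
|---|---|---|---|---|
| 10% | 0.01–0.02 | about 0 | 0.03–0.06 | 0.02–0.05 |
| 20% | 0.02–0.04 | about 0 | 0.04–0.10 | 0.03–0.09 |
| 30% | 0.03–0.06 | about 0 | 0.06–0.14 | 0.05–0.12 |
| 50% | 0.05–0.09 | about 0 | 0.11–0.22 | 0.10–0.19 |

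An all-waves likelihood analysis removes the bias when loss depends on observed scores. When loss depends on unobserved scores it removes little: for example, 0.216 falls to 0.191, a cut of 0.025 / 0.216 = 12%.

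**The case against.** The article is a condensed account. Missing-data handling may sit in an analysis plan that is not shown, and its absence here is no finding. That is accepted. The point rests on what the article does state: the method, and the one remedy for drop-out.

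A reader might infer more than the text supports in four places:

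- **That anyone with a missing wave is dropped.** This needs all waves in one model without imputation, which the article does not say. Run wave by wave, only those missing that wave or a covariate are lost. The day-50 drop-outs still go, and the single-step figures come from exactly that analysis.
- **That the Strava effect is biased, or that the protocol hypothesises alienation-driven drop-out from this trial.** The Introduction says only that alienation might explain drop-out seen elsewhere. Whether it predicts future use is posed as a question.
- **That leaving the app means leaving the study.** The documents do not say so. Participants receive credits for taking part, and someone may stop using Strava and still answer at day 50. The bias arises only where the two coincide.
- **That the comparison is by actual use.** The wording about participants who use an app explains why no feature has priority. It does not define an analysis set, and the same section allocates people at random.

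The sizes also depend on assumptions. The 50% case echoes an outside figure on new users, not a planning rate for this trial, and at 10 to 30% loss the bias is small beside d = 0.5. These objections limit the certainty and the size. They do not make a larger sample an answer to informative loss.

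**Conclusion.** The concern holds as a conditional risk. A complete-case method paired with over-recruitment alone does not address the kind of drop-out that the Introduction itself raises, and a better use of the planned data is available. If app leavers also stop answering, and leave because of worse scores, the comparison would tilt towards Strava by the amounts shown in the check. Those sizes rest on the assumed wave correlation, the assumed strength of the link between score and loss, loss driven by the day-10 score, and baseline adjustment. Loss driven by unobserved scores would give larger bias, most of which no standard all-waves analysis would remove. The documents do not establish that such bias will occur. This is a cheap improvement, not a defect that invalidates the trial.

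**What to change.** 1. Make the main analysis a linear mixed model for repeated measures, for each primary outcome and for the secondary alienation-empowerment outcome. Include all randomised participants by allocated condition, whatever their app use. Fit condition × wave, the baseline score and an unstructured covariance, and report the day-50 contrast.
2. To keep people with no post-baseline score in the model, treat baseline as a response with equal means across arms.
3. State that the already planned questionnaires continue to go to participants who stop using Strava.
4. Add a delta-adjusted missing-not-at-random sensitivity analysis for Strava drop-outs. A shift of δ in the missing scores moves the contrast by roughly the fraction missing × δ. As an illustration, at 30% loss a shift of 0.5 SD moves it by 0.3 × 0.5 = 0.15 SD.
5. Keep MANCOVA as a supportive analysis.
6. In Study 2, describe the comparison as between participants *allocated to use* and *allocated not to use* a self-tracking app, to match the random allocation.

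The cost is some wording and slightly more modelling, using questionnaires already planned. The main analysis would rely on data being missing at random given the observed waves, which is why items 3 and 4 are needed.
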